# The Communities Organizing for Power Through Empathy (COPE) Community-Based Intervention to Improve Adult Mental Health During Disasters and Crises: Protocol for a Stepped-Wedge Cluster Randomized Trial

**DOI:** 10.2196/63723

**Published:** 2025-05-20

**Keywords:** mental health, community-based group mental health intervention, disaster, community-based participatory research, stepped wedge cluster randomized trial, Gulf Coast

## Abstract

**Background:**

Severe weather events, exacerbated by climate change, can lead to hardships such as displacement, resource scarcity, and social network disruptions. Such disasters impact mental health, triggering conditions such as anxiety, depression, and posttraumatic stress disorder. For communities in the Gulf South, the increasing frequency of disasters often further exacerbates already disastrous levels of inequality. In this context, there is an urgent need for evidence-based, multilevel, community-based interventions to support individual and community mental health and resilience.

**Objective:**

This protocol describes the design of a community-based participatory research (CBPR) study to improve individual and community mental health in Gulf South communities by examining the implementation and effects of the multilevel, community-based intervention, Communities Organizing for Power through Empathy (COPE). Specifically, this study aims to (1) examine factors affecting the implementation, effectiveness, and adoption of the COPE intervention and (2) test its effects on mental health and community resilience. We hypothesize that participants in the COPE intervention will experience greater reductions in psychological distress (eg, perceived stress, anxiety, and depression); improvements in protective factors (eg, social support and coping self-efficacy); and community participation as compared with an attention control group.

**Methods:**

The Consolidated Framework for Implementation Research guides our analysis of data collected from surveys, fidelity and field notes, interviews, and focus groups to examine aim 1. We examine aim 2 primarily via a 2-arm pragmatic stepped-wedge cluster randomized trial (SW-CRT) with individuals (approximately n=300) in clusters (faith-based and secular community-based organizations; approximately n=15) in a disaster-prone community in the US Gulf Coast. The cluster-based design implemented in steps supports the community-based nature of the study where timelines differ by organization. A total of 5 self-assessments will be conducted both in person and via email at later time points. We will integrate mixed methods in our analyses for aim 1 by combining themes from interviews and focus groups with implementation measures, and for aim 2 by constructing a data matrix to combine findings from the SW-CRT with thematic analyses of field notes and interviews.

**Results:**

The SW-CRT is being conducted from June 2022 to June 2025. Recruitment began in April 2023, to conclude in spring 2025, to assess mental health, social support, and community resilience at 5 time points. Data analysis and dissemination of results are expected by spring of 2026.

**Conclusions:**

This protocol is among the first to use a CBPR approach to examine the implementation and effectiveness of a multilevel intervention on psychological distress and resilience. This study provides new insights into how CBPR can enhance intervention implementation research and expand the evidence on community-based mental health interventions during disasters. Policy makers should consider integrating CBPR approaches into disaster response frameworks to ensure culturally relevant and sustainable outcomes.

**Trial Registration:**

ClinicalTrials.gov NCT06093737; https://clinicaltrials.gov/study/NCT06093737

**International Registered Report Identifier (IRRID):**

DERR1-10.2196/63723

## Introduction

### Background

Exposure to severe weather events can have far reaching consequences as affected individuals and communities confront hardships such as displacement, property damage, and resource scarcity [1]. These catastrophic events also often disrupt social networks and community structures, further complicating recovery [2,3]. Climate change, linked to greater frequency of these severe weather events and environmental disasters, such as hurricanes and tropical storms, has increased the threat to communities across the globe [4]. For many communities, these events exacerbate already precarious living situations and accompanying high levels of psychological distress [5-7], often persistent across generations, as evidenced by higher levels of posttraumatic stress symptoms (PTSS) found among children [8]. In addition, individuals and communities have become so disconnected that the US surgeon general advisory in 2023 stated that the country was facing an “epidemic” of social isolation [9]. In this context of increasing risk, there is an urgent need for evidence-based multilevel interventions that support individual and community mental health. This protocol describes a study that aims to add to that evidence base, detailing a community-based participatory research (CBPR) approach to examining the implementation and effectiveness of the multilevel, community-based intervention, Communities Organizing for Power through Empathy (COPE) [10].

Designed to address the compounded psychological stresses that communities face during crises, COPE expands resources available to support communities during crises and disasters by integrating interventive and community-building components with training on providing support using elements of psychological first aid (PFA) and mental health first aid (MHFA) [11-13]. The COPE intervention is particularly important for the Gulf Coast region, where the enduring legacies of slavery and systemic racism have contributed to disastrous levels of inequality [14] and the impacts of climate change and frequency of disasters further exacerbate disparities [15,16]. CBPR is a collaborative approach to research that establishes structures to meaningfully engage affected communities in partnership with researchers in all aspects of the process [17-20]. The CBPR project that developed the COPE intervention is now in the implementation phase and aims to address this heightened need for mental health support in a context of limited access to services. Adapted from an intervention that has shown sustained reductions in PTSS for participant survivors of hurricanes Harvey and Maria [21], the COPE intervention uses group process, psychoeducation, and dynamic activities to strengthen individual and collective coping strategies, as well as individual and community relationships.

### Mental Health and Disasters

The mental health impact of environmental disasters is both profound and multifaceted [22,23]. Trauma and loss associated with disaster exposure can trigger a range of conditions, including anxiety, depression, and posttraumatic stress disorder (PTSD) [5,6]. Rates as high as 59% for clinical depression have been found among survivors after severe flooding in China, and as 70.5% for PTSD among survivors after Hurricane Sandy in New York [5]. Furthermore, the psychological effects experienced from a disaster can persist, seen in higher rates of mental health disorders observed years following the disaster [24]. A study conducted 3 years after Hurricane Katrina devastated the Gulf Coast and the city of New Orleans in the United States found that 33% of survivors reported probable PTSD symptoms [25]. Another conducted 12 years after Katrina found that 1 in 6 low-income survivors still reported symptoms of PTSD, and the rates of psychological distress remained higher than before the hurricane [26].

The adverse effects of a disaster are shown to be further exacerbated when individuals and communities already face deficits or inequalities in resources or supportive services, and particularly when those inequities have spanned generations [14,27-30]. Low-income families, older adults, people with disability, immigrants, children, those who are imprisoned [31,32], and women [33] are disproportionately impacted, often due to limited resources and infrastructure with which to effectively prepare for, respond to, and recover from disasters [28,34]. Limited financial or social resources, coupled with reduced access to basic health and mental health services, can impede capacity to rebound from such events [35]. This can lead to enduring psychological distress, deepening socioeconomic disparities, and a prolonged disruption of community cohesion and recovery [31,34,36].

The development of the COPE intervention and this study were motivated by our awareness that many of the factors associated with increased risk of experiencing adverse psychological outcomes after a disaster, such as prior trauma [37], limited income [27], and low levels of social and community support [38], are omnipresent in our community and the Gulf South. In addition, uncertainty and chronic stress associated with disaster exposure, frequent in the region, have been shown to exacerbate existing mental health conditions [39,40]. Studies have shown, however, that protective factors, including individual adaptive coping strategies [41-43], self-efficacy [44-46], and spirituality [47-50] interpersonal social support and relationships, and community or neighborhood cohesion [33,51], can reduce the likelihood of experiencing adverse mental health outcomes after a disaster. This study aims to examine whether the COPE multilevel intervention, designed to enhance individual protective factors (eg, adaptive coping), and delivered in a format designed to strengthen social capital (ie, interpersonal and community protective factors such as social support, relationships, and community cohesion), could improve individual mental health outcomes in communities with persistent high levels of inequity and disaster-related stress.

### Disaster-Related Mental Health Support Interventions

Mental health support services are important in all phases of a disaster (preparedness, response, and recovery) to help individuals and communities cope with trauma, prevent long-term psychological consequences, and support healthy recovery. In the preparedness phase, disaster mental health programs are designed to psychologically prepare individuals and communities for potentially traumatic events. Education and training interventions in this phase enhance the community’s capacity to respond to mental health needs if a disaster occurs [52].

One widely disseminated preparedness training, PFA, is designed to increase the capacity of non–mental health specialists to provide basic safety and stability to survivors during the response phase [11,53]. Core elements of PFA include addressing basic needs, mitigating harm, providing reassurance and safety, and connecting survivors to supports and services [11,54]. A similar training intervention, MHFA, is designed to equip nonspecialists with the knowledge and skills to identify and respond to individuals experiencing psychological distress [55]. Specifically, MHFA focuses on identifying signs of mental illness and substance abuse, providing basic psychological support, and connecting distressed individuals to professional support services [55]. Both PFA and MHFA primarily use didactic lectures and instruction focused on disseminating information instead of delivery methods that engage participants in group processing, interactive learning through hands-on activities, and reflection. Although MHFA and PFA have been shown to increase participant knowledge on providing mental health support to disaster survivors, research on how the knowledge and skills gained is deployed during disasters is limited [13,54].

During the disaster response phase, mental health services focus on the immediate needs of survivors [34,56]. Disaster mental health response efforts generally involve identifying and triaging individuals to crisis counseling services or providing immediate stabilization to distressed survivors [56]. However, crisis counseling varies widely in approach and method, making it difficult to standardize care and measure outcomes [56]. Psychological debriefing (PD), a brief intervention delivered by a mental health professional as a single individual or group session within 72 hours of a traumatic event, includes discussing, validating, and normalizing survivors’ trauma response [56]. There is mixed evidence on the effectiveness of PD: some studies suggest debriefing can reduce PTSS [57] and others have indicated PD may cause further distress [58].

The recovery phase focuses on the long-term mental health and well-being of survivors. It also contributes to preparedness and mitigation. Formal mental health treatment is one category of intervention provided to support survivors exhibiting clinical manifestations of distress [59]. Cognitive behavioral therapy, narrative exposure therapy, and other forms of psychotherapy have all been found to reduce clinical rates of PTSD, depression, and anxiety in disaster survivors [60,61]. Other mental health supports provided during the recovery phase include community-based wellness and resilience-building psychosocial interventions, generally designed for specific groups (eg, teachers, social service, or health care providers). One brief intervention, Caregivers Journey of Hope (CJoH), is designed to increase coping and reduce stress among disaster-affected social service providers [62]. It has been found to significantly reduce perceived stress and improve social support and knowledge of community resources [62]. Another intervention, Resilience and Coping for the Healthcare Community (RCHC), incorporates psychoeducation, action learning, and solution-focused strategies to reduce distress and increase social and peer support among health care providers [21,62,63]. A study assessing the effects of the RCHC among health care employees after hurricanes Harvey and Maria in 2017 found a significant likelihood of experiencing reductions in PTSS, anxiety, and secondary traumatic stress at the *P*<.01, *P*<.05, and *P*<.05 levels, respectively, at week 12 for those who received the RCHC as compared with a control condition [21]. Targeting both the recovery and preparedness phases, the COPE intervention being examined with this protocol adapted the RCHC for delivery to laypersons, incorporating illustrated materials to deepen conceptual understanding and foster dialogue across diverse literacy levels, content on historical trauma to acknowledge systemic factors, and sessions on supporting people in distress and identifying neighborhood resources to improve community response capacity [10].

Research examining the efficacy of disaster mental health interventions has primarily focused on the effectiveness of interventions designed to treat clinical diagnoses such as PTSD, anxiety, and depression [34,64], or on trainings that prepare individuals to provide basic psychological support [34,65]. Emerging evidence suggests community-based interventions, such as the CJoH and RCHC, improve individual mental health after the disaster [21,62]; however, more research is needed on their applicability across contexts and with diverse populations, as well as on how they affect individual mental health and community resilience [34,52]. In addition, as highlighted by Gil-Rivas and Kilmer [18], scholars have recommended “a CBPR approach to disaster preparedness and response that involves community-level organizing” as an effective strategy to strengthen community resilience in a culturally relevant and contextually appropriate fashion [66-68]. Better understanding the effectiveness and implementation of multilevel interventions designed for broad audiences that address mental health and well-being at the individual, interpersonal, and community levels is key to improving access during recovery [69].

### Rationale for the Study

The compounding psychological effects of successive disasters on the Louisiana Gulf Coast, including 5 named storms in the 2020 hurricane season followed by the catastrophic Hurricane Ida in 2021, in the context of the long-term stress of the global COVID-19 pandemic, brought to the foreground the need to consider mental health as a component of community resilience. Community resilience refers to a community’s capacity to prepare for, respond to, and recover from crises and disasters [70]. Important aspects of community resilience include strong community networks, local knowledge and response capabilities, and access to physical and mental health care [70].

Often, and particularly in the Gulf Coast region, it is neighbors and local community members who are the first to respond to a disaster [71]. This role that neighbors and local community members play in disaster response underscores the need for multilevel interventions to increase individual and community capacity to prepare for and cope in the aftermath of disasters. It also underscores the value of engaging community members in a CBPR approach to adapting and implementing those interventions. In response, the COPE curriculum [10] was developed via a CBPR project undertaken by the community organization Together Baton Rouge (TBR) and academic researchers. TBR is a 501(c)3 nonprofit and a broad-based organization [72,73], meaning that it is comprised of, and financially sustained by, other faith-based and secular organizations (community-based organizations [CBOs]) in the community that pay membership dues to support its work. This partnership structure thus provides a unique opportunity to test a distinct implementation design by delivering COPE at a variety of CBOs that are interconnected as members of the single committed partner organization, TBR.

This study responds to 2 primary questions about the COPE intervention model: (1) How do contextual factors affect intervention implementation? and (2) How does COPE affect individual, interpersonal, and community level well-being? We examined these questions using a pragmatic, stepped-wedge cluster randomized trial (SW-CRT) design with rolling enrollment. This design permits study of intervention effects in a context where individual randomization was not feasible given the group-based intervention and its delivery to individuals associated with the cluster (community institution) where they participate. In addition, the stepped roll out better supported the community-based nature of the study in which all clusters were not ready to deliver at the same time, and all expected to participate in the intervention.

### Aims and Hypotheses

In this paper, we describe the design of our mixed methods study that includes a pragmatic 2-arm SW-CRT [74] that examines the effectiveness and implementation of COPE, a group psychoeducational intervention designed to support individual and community mental health. The SW-CRT research design randomly assigns clusters (eg, communities and organizations) to transition from control to intervention in phases, until each eventually receives the intervention [74]. This research design supports phased community engagement and recruitment by sequentially introducing interventions, helping to reduce staff and organization burden. The aims of this SW-CRT are 2-fold. First, we aim to examine contextual factors, such as organization type and timing of delivery, to understand how they affect implementation, efficacy, and adoption of the COPE intervention. We hypothesize that cluster-level factors—such as organizational support, participant engagement, and facilitator training—and individual-level factors—such as age and education level—will influence feasibility, implementation, and acceptability of the COPE intervention. In addition, we hypothesize that the interrelationship between clusters as part of a larger organization will improve recruitment both at the cluster and individual level. Second, we aim to test the effectiveness of the COPE intervention [10], compared with an attention control arm (house meetings), in reducing mental health distress and strengthening coping, social support, and community engagement across 5 time points (Figure 1). We hypothesize that individuals who participate in the COPE intervention will report greater reductions in psychological distress symptoms (perceived stress, depression, and anxiety) than the attention control group, alongside significant increases in protective factors (coping self-efficacy, social support, and community resilience).

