## Methods

### Overview and Study Design

This study uses a pragmatic mixed methods approach to examining the effectiveness and practical relevance of COPE in a real-world context [75]. We will collect and examine qualitative data to address aim 1, capturing contextual information about cluster-level and individual-level factors that influence the feasibility, implementation, and acceptability of COPE. We will approach aim 2, the test of intervention effectiveness, using a SW-CRT with a rolling enrollment design. As a pragmatic 2-arm SW-CRT, the study has two conditions or arms: (1) the intervention arm, in which clusters of participants begin by engaging in the COPE intervention, and (2) the attention control arm, in which clusters of participants begin by attending “house meetings” (listening sessions) before switching to the COPE intervention. A cluster is defined as a single CBO (or in a rare case, a pair of related CBOs). Clusters are eligible to participate if they are CBO members of TBR. Steps are clusters grouped by availability (ie, feasible start date as provided by CBO leadership). At the initiation of a step and before participant enrollment, clusters are randomized into study arms.

As a SW-CRT, every cluster will provide before and after observations, and will switch from control to intervention, but not at the same point in time (Figure 1) [74]. At study outset, clusters are assigned by the first author to 1 of 5 sequential steps: 2 in step 1, 4 in steps 2 and 3, and 6 in steps 4 and 5 (Figure 1). At the initiation of a step, clusters will be randomized by the first author into the intervention and control arms using a random number generator. Allocation into intervention or control arms will not be concealed at either the cluster or individual level, nor will clusters or participants be blinded, as doing so is not feasible given the group-based nature of the intervention and community-based nature of the study implementation. We will include controls to account for temporal and enrollment differences. Presurvey data collection will occur immediately before the start of the intervention within each cluster. After the third data collection time point, the clusters in the attention control arm will switch to receive the COPE intervention (see Figure 1 for the design timeline).

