As shown in Figure 4, the COPE series consists of the primary session 1 (C1, 4 h), focused on recognizing stress in oneself and developing healthy coping strategies while simultaneously building relationships to increase social and community support, and 2 additional follow-up sessions (C2 and C3, 90 min each). Each workshop session engages participants in group exercises that provide information in stress and trauma, skills training on recognizing and supporting individuals exhibiting distress, identifying and developing healthy coping strategies, and identifying and building community-based support.

The second session (C2) focuses on supporting individuals in distress and the third (C3) focuses on building community support. More specifically, session 2 (C2) centers skill building for nonspecialists to increase their capacity to provide basic psychological support to individuals in distress, and it incorporates an interactive role play to provide an opportunity to practice skills learned. Session 3 (C3) centers community resilience, engaging participants in an interactive discussion to name community assets and then map those available within the geographic area of their institution. COPE has been standardized in a single manualized curriculum with accompanying large-format illustrated posters laminated for interactive use and participant workbook [10]. The COPE participant workbook has been translated into Spanish and validated using back translation. For the SW-CRT, assessments will be conducted before each session.

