### Attention Control Arm: House Meetings

Parallel to the intervention arm, participants in clusters randomized to the control arm will complete assessments before content delivery at the first 3 time points. After the first 2 assessments, they will participate in house meetings—group deliberative conversations, sometimes referred to as listening sessions—following a model regularly practiced by TBR [84,85] before participating in the COPE intervention at their third meeting and just after completing their third assessment. The house meeting is a group session that lasts approximately 1.5 hours and engages participants in a discussion about a specific question posed by the facilitators. At the first house meeting, and after administering the first assessment, participants are prompted to discuss “How are you a caregiver in your everyday life? What does it mean to you to be a caregiver?” or a similar question. Each participant is encouraged to share at least once. The facilitator is not necessarily a mental health professional, and no therapy is provided. At the end of the house meeting, participants are reminded of the date for the next meeting. The second house meeting follows the same protocol with a modified prompt question. After completing the third assessment, participants engage in the COPE intervention.

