**Process evaluation**				
	Acceptability of Intervention	—	Acceptability	Weiner et al [86], 2017
	Intervention Appropriateness	—	Appropriateness	Weiner et al [86], 2017
	Feasibility of Intervention	—	Feasibility	Weiner et al [86], 2017

^a^Not applicable.

To address aim 2, we will collect cohort data on the outcome measures at the 5 assessment time points of the SW-CRT: baseline (T1), before session 2 (T2; 1 m after baseline), before session 3 (T3; 2 m after baseline), after the series (T4; 1 month after session 3), and 6 months after the series (T5). Figure 1 provides a visual of the design and timeline of survey measures. As the control arm switches to the COPE intervention after the T3 assessment, assessments pause until 1 month after session 3 so that T4 assessments align (Figure 1). Both arms complete the T5 assessment 6 months after session 3. As part of the CBPR process, the CBPR strategy team deliberated on the outcomes and measurements, coming to consensus on the final survey.

The primary outcomes and their measures assess individual mental health. Perceived stress is assessed with the Perceived Stress Scale (PSS), a 10-item scale that measures the degree to which a person rates situations as stressful [88], for example, how often respondents find their lives “unpredictable,” “uncontrollable,” or feel “overloaded.” Responses are scored on a 5-point Likert scale ranging from 0 (never) to 4 (very often). Total PSS scores range from 0 to 40, with higher scores reflecting higher perceived stress [91]. The 10-item Perceived Stress Scale has high internal reliability (Cronbach α=0.78-0.90) and has been translated and tested in >25 languages [88,91]. Depression, anxiety, and stress are measured with the Depression, Anxiety, and Stress Scale (DASS-21), a set of 3 self-report scales [87]. The 21 DASS-21 items ask about the presence of symptoms over the past week on a scale from 0 (did not apply to me at all) to 3 (applied to me very much or most of the time) [92,93]. Depression scores range from 0 to 4 (normal), 5 to 6 (mild), 7 to 10 (moderate), 11 to 13 (severe), and >14 (extremely severe). Anxiety scores range from 0 to 3 (normal), 4 to 5 (mild), 6 to 7 (moderate), 8 to 9 (severe), and >10 (extremely severe). Stress scores range from 0 to 14 (normal), 15 to 18 (mild), 19 to 25 (moderate), 26 to 33 (severe) and >34 (extremely severe). The DASS-21 has shown high internal reliability (Cronbach α=0.72-0.91) [92-94].

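### Aim 2 compares COPE with house meetings across five time points, but the concurrent randomised contrast ends at T3, after sessions 1 and 2 only

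*Protocol article*

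**What the plan says.** The second aim in *Aims and Hypotheses* is to test COPE against house meetings "in reducing mental health distress and strengthening coping, social support, and community engagement across 5 time points". COPE is a three-session series (*Intervention Arm: COPE*): session 1 lasts 4 hours and sessions 2 and 3 last 90 minutes each. "Session 3 (C3) centers community resilience", and the same section says that "assessments will be conducted before each session".

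*Study Outcome Measures* places the later surveys "before session 3 (T3; 2 m after baseline), after the series (T4; 1 month after session 3), and 6 months after the series (T5").

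For the controls, *Overview and Study Design* says: "After the third data collection time point, the clusters in the attention control arm will switch to receive the COPE intervention". *Attention Control Arm: House Meetings* is more exact: they attend two house meetings "before participating in the COPE intervention at their third meeting and just after completing their third assessment". After the switch, "assessments pause until 1 month after session 3 so that T4 assessments align". Both arms take T5 six months after session 3.

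*Planned Analyses, Aim 2* specifies a linear mixed model with fixed effects for arm, time and covariates. It codes each participant by the condition in force at each survey and recognises that controls count as intervention at T4 and T5. It adds a sensitivity analysis of T1-3 against T4-5, said to show effects while controls are still unexposed.

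**The concern.** The aim names a three-session intervention, a control arm and five surveys, which reads as a controlled comparison at all five. The schedule supplies one at T2 and T3 only, and the COPE arm completes its series after T3.

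At stake is what the trial may claim. A change at T4 or T5 could be reported as an effect of the whole series or as six-month persistence, and a rise in community resilience (CART) after session 3 as an effect of that session. Each would be change over time with no randomised unexposed group beside it. Conversely, a benefit that needs all three sessions would be largely or wholly missed by the primary coefficient.

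*Potential Limitations* does not say that the controlled contrast stops at T3. It mentions difficulty in assessing effectiveness beyond 6 months, which a reader could take to mean that effects up to 6 months are tested against control.

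**Working it through.** **1. Exposure at each survey.** From *Intervention Arm: COPE*, *Attention Control Arm: House Meetings* and *Study Outcome Measures*:

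| Survey | COPE arm has had | Control arm has had | Unexposed control? |
|---|---|---|---|
| T1 | nothing | nothing | yes (baseline) |
| T2 | session 1 | house meeting 1 | yes |
| T3 | sessions 1-2 | house meetings 1-2 | yes |
| T4 | sessions 1-3 | sessions 1-3 | no |
| T5 | sessions 1-3 | sessions 1-3 | no |

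Hours of COPE by T3: 4 + 1.5 = 5.5. Full series: 4 + 1.5 + 1.5 = 7. So 5.5/7 = 79%. None of the two post-series surveys has an unexposed comparator.

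**2. The plan's own power figure.** *Sampling Strategies and Sample Size* gives effect 0.3, five time points, ICC 0.10, within-person correlation 0.3, and 15 sites of 20. I used generalised least squares on cluster-by-visit means, with random cluster and person intercepts, total variance 1, categorical visits and one constant effect. My assumptions are two-sided alpha 0.05, 8 versus 7 clusters and no random slopes. Under three readings of the within-person correlation, power is 93-96% (normal approximation) or 89-93% (t with 13 df). The stated 80% target is met. That figure credits T4 and T5 through a single constant effect from session 1 to six months after the series.

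**3. Which effects can be estimated.** With a separate effect at each of T2 to T5 plus arm-common visit effects, the design matrix has 9 columns and rank 7. T2 and T3 are estimable; T4 and T5 are not. Replacing visit by months since step start gives the same answer.

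**4. What a late effect adds to the primary coefficient.** Exposure coding is 0,1,1,1,1 (COPE) and 0,0,0,1,1 (control). Take a true effect of 0.30 present only at T4 and T5, in both arms. The weights below use total within-person correlation 0.3.

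- *Categorical visits.* The T4 and T5 weights are -0.301 each in the COPE arm and +0.301 each in the control arm. Contribution: 0.30 × (-0.301 - 0.301 + 0.301 + 0.301) = 0. The cancellation does not depend on the variance inputs, because fitting a visit effect forces the weights within each visit to sum to zero.
- *Linear visit number.* COPE weights are -0.049 and -0.386; control weights are +0.407 and +0.112. Sum 0.084 × 0.30 = 0.025; 0.026 before rounding the weights.
- *Linear months.* The assumed schedule has T4 and T5 at months 3 and 8 (COPE) and 5 and 10 (control). COPE weights are +0.211 and -0.334; control weights are +0.425 and -0.052. Sum 0.250 × 0.30 = 0.075.

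The two non-zero values arise because a straight line cannot absorb a late shift common to both arms.

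**5. The sensitivity analysis.** T1-3 against T4-5 compares earlier with later surveys. Effects while controls are unexposed require COPE against control within T1-T3, which is a different contrast.

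**6. Precision of the T1-T3 contrast.** Same model as step 2, total within-person correlation 0.3: standard error 0.109, against 0.087 with five visits. Over the three readings, T1-T3 power is 79-84% (normal) or 72-78% (t). If the cluster effect is allowed to drift between visits (autocorrelation 0.8, my assumption; total correlation 0.3; normal), power is 80% with five visits and 65% with T1-T3.

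**The case against.** The switch is disclosed in several sections, is inherent in a design where every cluster receives COPE, and is justified because all clusters expected to take part. The phrase on five time points stands in the aim, beside a pointer to the timeline figure, and the hypothesis that follows names no horizon. The model is announced as covering within-group as well as between-group differences. No sentence claims a controlled six-month or session 3 effect, and the Discussion asks for further studies of long-term effects. All of this stands. It makes the point one of claim and analysis, not of a hidden or improper design.

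Four stronger readings are tempting, and the documents do not support them.

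- *That T4 and T5 are never set against any unexposed group.* Earlier control surveys, or controls in other steps overlapping in calendar time, could serve. But steps are formed by availability, so comparisons across steps are not randomised. Whether they are even estimable depends on step spacing, which the text does not give: with equally spaced steps and the assumed monthly schedule they were estimable at 2 or 3 months and not at 4 to 6.
- *That a late effect always contributes exactly zero.* This needs categorical visits. The plan says only time, with random slopes for time.
- *That CART change can come only from session 3.* All three sessions are described as addressing community support, and session 1 is the primary one, so T2 and T3 carry controlled information on CART.
- *That the trial has no randomised evidence on COPE.* It has a randomised contrast on every outcome at T2 and T3.

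The objection leaves two things unanswered: the aim is worded as a five-point comparison with control, and the sensitivity analysis cannot deliver its stated purpose.

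**Conclusion.** The point holds. Within a step, the concurrent randomised contrast with unexposed controls covers session 1 (T2) and sessions 1-2 (T3), that is, 5.5 of 7 hours. Session 3, the full series and the T4/T5 outcomes, including CART after session 3, have no such comparator. This follows from the schedule alone and does not depend on any power figure.

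The effect on the primary coefficient depends on the model: a 0.30 effect confined to T4/T5 adds 0 with categorical visits and about 0.03 to 0.08 with linear time. The upper value rests on an assumed calendar of monthly sessions. T4 and T5 do sharpen the primary estimate, but only if the effect is constant from session 1 to six months after the series.

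**What to change.** 1. *Aims and Hypotheses* and *Planned Analyses, Aim 2*: state that the randomised effect is COPE session 1 (at T2) and sessions 1-2 (at T3) versus house meetings. Keep the five time points as a description of data collection, separate from the comparison with control.
2. *Planned Analyses, Aim 2*: replace the T1-3 versus T4-5 sensitivity analysis with a between-arm contrast restricted to T1-T3.
3. Report T4 and T5, including CART after session 3, as uncontrolled within-arm change.
4. *Potential Limitations*: state that no controlled claim is made for session 3, the full three-session series or six-month persistence.

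The cost is a narrower claim and a T1-T3 analysis less precise than the five-visit model (standard error 0.109 against 0.087 under the inputs above). No data or participants are added, and the control switch stays as planned.
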